**Figure 1 F1:**
[figure not shown]
Trial flow chart. ACET: arm crank exercise training.

### Outcomes

#### Demographics

Demographics (age, sex, height, weight, body mass index [BMI], ethnicity, postcode and level of education), and medical (eg, comorbidities) and treatment history of the participants will be recorded (cause of injury, duration, level of injury, severity of injury and sensory and motor scores according to the International Standards for Neurological Classification of Spinal Cord Injury (ISNCSCI)).^42^ Information regarding the duration and types of standard in-patient rehabilitation care will be collected from hospital records and patients’ exercise diaries during the trial. See table 1 for the assessment timeline. Detailed outcomes are listed below.

**Table 1 T1:** Timeline for enrolment, interventions and assessments

		Study period					
		**Enrolment**	**Pre-allocation**	**Allocation**	**Postallocation**		
Timepoint		**−T0**	**T0**	**Allocation**	**T1**	**T2**	**T3**
Enrolment							
Eligibility screen		X					
Informed consent		X					
Allocation				X			
Intervention							
ACET							
Assessments							
Demographics, injury information	Questionnaire	X					
Independence	SCIM-III	X				X*	X
Sitting balance kinematics and HDEMG	Unsupported static sitting		X		X	X	X
	Forward reaching		X		X	X	X
	Lateral reaching		X		X	X	X
	Arm raise		X		X	X	X
	Rapid shoulder flexion		X		X	X	X
Corticospinal excitability	Motor evoked potentials		X		X	X	X
Motor recovery and impairment	ISNCSCI motor score and AIS	X	X		X	X*	X
Neuropathic pain	DN4		X		X	X	X
Depression	PHQ-9		X		X	X	X
Anxiety	GAD-7		X		X	X	X
Self-efficacy and motivation	TRSQ and PCS modified		X		X	X	X
Physical activity	GENEActive				X	X	
Leisure activity	LTPAQ-SCI						X
Quality of life	SF-36						X
ACET for early rehabilitation	Qualitative focus group						X

Note: (X*) SCIM-III and ISNCSCI at T2 or discharge.

ACET, arm-crank exercise training; AIS, American Spinal Injury Association Impairment Scale; DN4, Neuropathic pain four questions; GAD-7, general anxiety disorder; HDEMG, high-density surface electromyography; ISNCSCI, International Standards for Neurological Classification of Spinal Cord Injury; LTPAQ-SCI, leisure time physical activity questionnaire for people with spinal cord injury; PCS, perceived competence scales; PHQ-9, Patient Health Questionnaire; SCIM-III, The Spinal Cord Independence Measure; SF-36, 36-Item Short Form Survey; TRSQ, Treatment Self-Regulation Questionnaire.

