In the early stages following injury, research in animals with SCI showed sprouting of corticospinal axons rostral and caudal to the lesion site, forming alternative neural circuits to maintain supraspinal influence on motor neurons below the injury.^20^,^22^ Exercise interventions in rats with SCI increase the levels of neurotrophins that overcome myelin-derived axon growth inhibitors^23^ and promote synaptic plasticity in the spinal cord, creating new circuits to restore function.^24 25^ Similarly, evidence in humans with SCI has suggested the benefits of early motor training for promoting recovery of limb function.^26^,^28^ Given that neural pathways undergo extensive reorganisation during the early stages of SCI,^29^ particularly when the injury is incomplete,^30^ it is logical to hypothesise that the therapeutic effects of early ACET will be even greater in individuals with subacute SCI.

In addition to the physical benefits, exercise has been shown to improve pain and psychological symptoms in both general and clinical populations.^31 32^ People living with SCI experience higher levels of neuropathic pain,^33^ anxiety and depression compared with those without.^34^ However, low levels of exercise self-efficacy (ESE) in people with SCI^34^ on often decrease adherence and maintenance to exercise, thus hindering recovery.^35^

We are not aware of any studies investigating self-directed ACET and its effects on trunk control in individuals with subacute SCI. Hence, the primary aims of the study are to investigate the effects of ACET on volitional control of the trunk, and the neurophysiological mechanisms underpinning these effects in adults with subacute incomplete SCI. The secondary aims of the study are to evaluate short- and long-term benefits of the ACET on neuropathic pain, psychological well-being, and physical activity in this population. Additionally, self-efficacy and motivation of individuals with SCI for engaging in the ACET will be examined as potential predictors of adherence and the outcomes. This is important because people with SCI often experience higher levels of neuropathic pain,^33^ anxiety and depression compared with those without.^34^ However, low levels of ESE in people with SCI^34^ on often decrease adherence and maintenance to exercise, thus hindering recovery.^35^ Furthermore, we will investigate long-term translational effects of ACET on leisure time physical activity and health-related quality of life.

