The objectives of the study are:

To assess static and dynamic sitting balance after 8 weeks of ACET in individuals with subacute incomplete SCI.To examine training-induced changes in activation of the ES during static and dynamic sitting balance tasks and excitability of the corticospinal axons projecting to the ES in individuals with subacute incomplete SCI.To evaluate neuropathic pain, psychological well-being, physical activity, independence, muscle strength and health related quality of life in individuals with a subacute incomplete SCI.To predict adherence to the ACET and outcomes using individuals’ self-efficacy and motivation.

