### Study population and sample size

The sample size was based on the effect size drawn from the feasibility study reporting an improvement in angular displacement of the trunk during forward reaching with ACET compared with the standard of care, with a large effect size (Cohen’s d = 0.85). An a priori power calculation suggested that a sample size of 46 patients with SCI, 23 in each group, is sufficient to detect a between-group difference for the primary outcome measure, using an independent t-test with 80% power and a 5% level of significance. To account for a 6-month follow-up after discharge, a 30% conservative dropout rate was considered. Hence, 60 participants in total will be recruited for this study.

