
### Assessments

The study has four assessment periods—baseline (T0), 4 weeks (T1), postintervention (T2), and 6 months follow-up (T3). Assessments from T0 to T2 are expected to occur while participants are still within 12 months postinjury. However, the T3 assessment may occur during the chronic phase of SCI for some participants. We expect that all participants will have the baseline and 4 weeks assessments conducted at the spinal units. We also anticipate some participants will have the postintervention and 6 months follow-up assessments at the spinal units or at the University of Birmingham, whichever is more convenient to them.

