### Randomisation

All participants will undergo one baseline assessment and one 4-week assessment to estimate individuals’ spontaneous recovery rate. After the 4-week assessment, participants will be randomly allocated (1:1) to an ACET group or a standard care control group using a minimisation randomisation^41^ to balance covariates of level of injury and classification of injury between groups. The procedure will start from the first participant being allocated to a study group at random. For each subsequent participant, we determine which study group would lead to better balance between the groups in the variables of interest. The randomisation will be performed by [name] who will not be involved in recruitment of participants. However, it is not achievable in this study to blind participants or researchers conducting the assessments given the type of the intervention and resources available. Figure 1 illustrates the trial flow chart.

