### Statistical analyses

Statistical analyses will be performed using the latest version of SPSS available at the time of analysis (IBM, Armonk, NY, USA). The distribution of the continuous variables will be tested for normality using the Shapiro-Wilk test and appropriate descriptive parameters will be reported and statistical tests will be applied accordingly. A mixed-model two-way repeated measures ANOVA, with group as the between-participant factor and time as the within-participant factor, will be used to compare outcome measures. This analysis will be performed according to the intention to treat approach. Post hoc tests will be applied where there is a main effect. Significance level will be set at 0.05 for all statistical tests. For the data that are normally distributed, effect sizes of partial eta squared (η2p) or Cohen’s d will be calculated. Additionally, potential confounders (eg, age, days since injury) will be included in the analysis. Subgroup analyses (eg, based on AIS classification) will also be performed if appropriate.

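### SF-36 quality of life is scheduled only at T3, so the comparison cannot be adjusted for baseline quality of life and participants lost earlier contribute no SF-36 data

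*Protocol article*

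**What the plan says.** Quality of life is part of the third objective in the Introduction: "To evaluate neuropathic pain, psychological well-being, physical activity, independence, muscle strength and health related quality of life in individuals with a subacute incomplete SCI". No time point is attached there. The aims are more specific and speak of "long-term translational effects of ACET on leisure time physical activity and health-related quality of life".

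The Assessments section gives the visits: "The study has four assessment periods—baseline (T0), 4 weeks (T1), postintervention (T2), and 6 months follow-up (T3"). The Randomisation section places allocation after T1: "After the 4-week assessment, participants will be randomly allocated (1:1) to an ACET group or a standard care control group".

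In Table 1 (under Demographics) the row reads "Quality of life SF-36", with the single mark in the last column, T3. The Health-related quality of life paragraph under Secondary outcomes describes the scales and the two summary measures but adds no other visit. The DN4, PHQ-9, GAD-7 and self-efficacy and motivation rows are each marked at T0, T1, T2 and T3.

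The Statistical analyses section plans a repeated measures ANOVA, "with group as the between-participant factor and time as the within-participant factor, will be used to compare outcome measures". It states intention to treat and says that potential confounders, with age and days since injury as examples, will be included. The Abstract also names Student's t-tests. On attrition, the sample size section says: "To account for a 6-month follow-up after discharge, a 30% conservative dropout rate was considered".

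**The concern.** The trial means to attribute a long-term quality-of-life effect to ACET but takes one SF-36 reading per participant, at the visit with the most expected loss. Three things follow.

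- No pre-allocation score is available as a covariate. For a continuous patient-reported outcome in a small trial, the baseline value of the same scale is usually the most useful covariate.
- A single visit has no within-participant time factor, so the group-by-time model does not apply to this outcome.
- A participant lost before T3 has no SF-36 data. The protocol commits to intention to treat, but there is no earlier SF-36 value from which a model could draw information, and no way to see directly whether those lost differed in quality of life.

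A missing baseline cannot be recovered once a participant has been allocated, so the gap becomes permanent with each allocation.

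**Working it through.** **Inputs from the protocol article.** Total 60, allocated 1:1; 46 evaluable (23 per group); d = 0.85 for the primary outcome; 80% power; 5% significance; 30% dropout (all from Study population and sample size). SF-36 at T3 only (Table 1).

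**Assumed input.** The correlation r between pre-allocation and T3 SF-36 is not in the documents. The range used is 0.3, 0.5 and 0.7.

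**Step 1: reproduce the plan's own figure.** A two-sided independent t-test (noncentral t) with d = 0.85, alpha 0.05 and power 0.80 needs n = 22.73, rounded up to 23 per group, 46 in total. Power at 23 per group is 0.805. The stated 46 is reproduced, so the same method is used below. The 60 matches 46 × 1.3 = 59.8. The protocol states no figure for SF-36.

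**Step 2: participants with an SF-36 value.** With the allowed loss, 60 × (1 − 0.30) = 42, or 21 per group. The other 18 have no SF-36 value at any visit.

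**Step 3: detectable difference without a covariate.** At 21 per group, two-sided alpha 0.05 and 80% power, the detectable standardised difference is 0.886.

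**Step 4: detectable difference with a baseline SF-36 covariate.** Adjustment multiplies the residual variance by (1 − r²), so the detectable difference becomes 0.886 × √(1 − r²). The degree of freedom spent on the covariate is ignored. The last column is power for an illustrative true difference of d = 0.5, which is not a figure from the protocol.

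| r | Residual variance left | Cut in variance | Detectable d | Power at d = 0.5 |
|---|---|---|---|---|
| none | 1.00 | 0% | 0.886 | 0.35 |
| 0.3 | 0.91 | 9% | 0.845 | 0.38 |
| 0.5 | 0.75 | 25% | 0.767 | 0.45 |
| 0.7 | 0.51 | 49% | 0.633 | 0.60 |

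**Step 5: size of an unseen imbalance.** With 21 per group, the standard deviation of the chance difference in baseline means is √(2/21) = 0.31 SD. The standard error of the T3 comparison already allows for this. A baseline score would let part of it be removed.

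**Step 6: fit of the planned model.** Group by time needs at least two visits. SF-36 has one, so what remains is a between-group comparison at T3, with or without covariates.

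**The case against.** The strongest reply is that measuring at T3 only suits the question asked. The aim is a long-term effect on leisure activity and quality of life, and both LTPAQ-SCI and SF-36 are scheduled at T3 alone. The protocol claims no immediate post-training effect on quality of life. With complete follow-up, comparing randomised groups at T3 is unbiased without a baseline. All of this stands, so the point is about precision and missing data.

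Several stronger readings are tempting and not supported:

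- A reader might infer that the comparison is unadjusted. The Statistical analyses section includes other covariates, and minimisation balances level and classification of injury. Only adjustment for baseline SF-36 is ruled out.
- A reader might infer that no planned test applies. The Abstract names t-tests, so a single-visit comparison has a method.
- A reader might infer that chance imbalance would invalidate a T3 difference. It would not, because the test's standard error covers it.
- A reader might say that quality of life is not measured after training. T3 is after training; the missing post-training reading is the one at T2.

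It is also fair to say that PHQ-9, GAD-7 and DN4 at T0 and T1 could serve as covariates and could be used to compare those lost with those retained. They would recover part of what a baseline SF-36 offers, so the gains in the table are upper figures for each r. They do not measure quality of life itself.

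Finally, at r = 0.3 the detectable difference moves only from 0.89 to 0.85, and the trial was not sized for SF-36.

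**Conclusion.** The point holds as a modest design weakness in one secondary outcome. It is neither a contradiction in the protocol nor a source of bias under complete follow-up. The schedule rules out adjustment for baseline quality of life, rules out the group-by-time model for SF-36, and leaves no SF-36 information on participants lost before T3.

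At 21 per group the detectable difference is 0.89 without covariates, against about 0.85, 0.77 or 0.63 with a baseline score. This rests on the full 30% loss occurring equally in both groups, a two-sided t-test, and correlations that are assumed rather than documented. The real gain would be smaller than these figures once other covariates are included. A null T3 result should be read as imprecise, not as uninformative. The change is still worth making because it is cheap and a baseline cannot be collected afterwards.

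**What to change.** 1. Add the SF-36 to the questionnaires already given at a pre-allocation visit. T0 is before allocation in both the Randomisation section and Table 1. T1 is closer to the start of training and could serve instead, but Table 1 heads it as post-allocation while the Randomisation section allocates after it. Those two places must be reconciled first.
2. Preferably add it at T2 as well, so that participants lost between T2 and T3 still contribute post-allocation information.
3. In Statistical analyses, state that the T3 summary scores are compared between groups with the pre-allocation score as covariate, using a likelihood-based model for repeated measures that includes T2 if it is collected.
4. If the schedule cannot change, state that SF-36 is compared at T3 only, name the covariates (for example the pre-allocation PHQ-9, GAD-7 and DN4 scores), and report those scores for participants with and without T3 data.

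**Cost.** One more questionnaire at one or two existing visits and an amendment to Table 1, with no new visit, staff or procedure. The downside is a modest added burden. Some items also fit in-patient life less well, which may lower the correlation with T3 and with it the gain.

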#### Primary outcome measure

The primary outcome of the study is trunk control, assessed by:

*1. Volitional control of the trunk*

*Static and dynamic sitting balance*. Sitting balance will be assessed using the following tasks: unsupported sitting for 30 s, forward and lateral reaching,^12 43^ bilateral voluntary arm raise^44^ and rapid shoulder flexion.^12^ Participants will perform each task five times while seated on a plinth with their trunk unsupported, feet flat on the floor, hips and knees positioned at 90°, and the popliteal fossa approximately a palm’s width away from the edge of the plinth.

For the unsupported sitting task, participants will be instructed to sit unsupported as stable and upright as possible for 30 s (figure 2A). For the multidirectional reaching tasks (figure 2B and C), participants will be asked to sit in an upright position and use the less affected arm to reach forward and to the side as far as possible without losing balance. For the voluntary arm raise task (figure 2D), participants will be instructed to hold a resistance band with both hands and move the band up by flexing the shoulder joints to the maximum active range of motion. A rapid shoulder flexion task will be used to assess anticipatory and compensatory postural adjustments, whereby participants will, while sitting, raise their arms to a horizontal outstretched position as quickly as possible in response to a short, sharp verbal cue (figure 2E). Movement of the upper limbs and trunk will be captured in 2D videos recorded with a camera in 1080 p at 30 frames per second (iPad mini fifth generation, Apple, CA, USA). The camera will be placed at the angle perpendicular to the movement plane. Furthermore, the kinematics of the trunk will be recorded at 100 Hz using an inertial measurement unit (IMU)^45^; (Sessantaquattro+, OT Bioelettronica, Turin, Italy) placed at the fourth thoracic spinous process (figure 3). Sitting posture (spinal curvature at rest),^46^ reaching distance,^12^ angular displacement of the trunk^47^ and range of motion of the shoulder joints^44^ will be analysed from the 2D videos.

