*Neuromuscular control of the trunk*. Muscle activity of trunk muscles during seated balance tasks, as measured with high-density surface electromyography (HDEMG). Activity of the lumbar ES during seated balance tasks (figure 2) will be recorded using HDEMG which contains multiple small electrodes in a large electrode grid. HDEMG is a non-invasive technique and provides a topographic representation of muscle activity.^48 49^ This methodology is suitable for investigation of neuromuscular function of paraspinal muscles (ie, ES) which have multiple muscle fibres covering several levels of the spine and are innervated by multiple spinal nerves from the adjacent spinal levels.^50^ EMG recording from a larger area of the ES, as opposed to the bipolar EMG, may capture changes in regional distribution of activation across the spinal levels of the ES, providing new knowledge of recovery of trunk muscles in humans with SCI. Semi-disposable HDEMG grids (HD08MM1305, OT Bioelettronica) consisting of 64 oval-shaped electrodes arranged in 13 rows by 5 columns, minus the top left corner (figure 3; 1 × 1.5 mm electrode, 8 mm interelectrode distance), will be used to record lumbar ES activity. An adhesive foam (FO108MM1305, OT Bioelettronica) will be attached to the grid and its cavities will be filled with conductive paste (AC Cream, Spes Medica, Genoa, Italy). The skin over the muscle belly will be shaved, gently abraded with paste (Nuprep Skin Prep Gel, Weaver and Company, CO, USA), and cleaned with water to remove any residue from the paste. The grid will be placed on the ES in parallel with the lumbar spine, with the top edge of the grid placed 2 cm away from the centre of the 12th thoracic spinous process, and the bottom edge extended in the caudal direction to approximately the 4th lumbar spinous process (figure 3). One reference electrode (Ambu WhiteSensor WS, Ballerup, Denmark; 36 mm × 40 mm) will be placed on the seventh cervical spinous process and connected to the Sessantaquattro+, and a second ground electrode will be placed unilaterally over the iliac crest for a bipolar EMG system placed on the deltoid. An adhesive electrode (19.8 mm × 35 mm) of a bipolar EMG system (Delsys Bagnoli-2 EMG system) will be placed on the muscle bellies of the anterior deltoid (AD) of the less affected arm to record AD activity during the arm raised task. HDEMG will be recorded in monopolar mode with an amplifier (256 V/V gain; Sessantaquattro+, OT Bioelettronica) and digitised at 2000 Hz using a 16-bits A/D converter (10–500 Hz bandpass filter, input resistance 100 kΩ). Bipolar EMG (pre-amplified x1,000, band-passed filtered 20–450 Hz) will be recorded simultaneously via an isolated auxiliary input device (ISO-AUXSP, OT Bioelettronica), operating a 0.5 V/V gain alongside HDEMG using OT Biolab software (OT Bioelettronica) and stored in a local computer for postprocessing purposes. Root-mean-square (RMS) amplitudes and the centroid of RMS activation of the lumbar ES will be analysed.

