
*Corticospinal axons excitability of the ES*. To assess the excitability of the corticospinal axons projecting to the ES, high-voltage electrical stimulation (Digitimer stimulator, DS7AH, UK; square wave pulse, pulse duration 200 μs) will be applied at the cervicomedullary junction to elicit motor evoked potentials (CMEPs) in the ES^16 51^ when participants are seated in their preferred comfortable position. Between 10 and 15 CMEPs will be recorded and averaged. Participants will be asked to relax initially, but the Jendrassik manoeuvre will be introduced to assess if little or no response in the ES is observed. The Jendrassik manoeuvre, where a participant will clench their teeth and flex fingers in a hook shape, has been shown to facilitate corticospinal excitability.^52^ Peak-to-peak amplitudes and latency of the averaged CMEP will be calculated.

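### The sample size treats the primary outcome as one variable, but the outcomes section lists eight named parameters under the primary heading, with every test at 0.05

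*Protocol article*

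**What the plan says.** Three sections of the Protocol article bear on this point.

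- **Study population and sample size.** The calculation rests on a feasibility result, "an improvement in angular displacement of the trunk during forward reaching", with Cohen's d = 0.85. It gives 23 per group for an independent t-test at 80% power and 5% significance. The section speaks of the primary outcome measure in the singular.
- **Primary outcome measure.** The text reads "The primary outcome of the study is trunk control, assessed by", followed by two numbered components. The first, volitional control, covers five tasks: "unsupported sitting for 30 s, forward and lateral reaching", then arm raise and rapid shoulder flexion. The video variables run from "Sitting posture (spinal curvature at rest") through reaching distance and trunk angular displacement "and range of motion of the shoulder joints". The second component is neurophysiological. For high-density EMG, "Root-mean-square (RMS) amplitudes and the centroid of RMS activation of the lumbar ES will be analysed". For corticospinal excitability, "Peak-to-peak amplitudes and latency of the averaged CMEP will be calculated". The secondary outcomes heading comes only after both components, and its numbering starts at item 3.
- **Statistical analyses.** A group-by-time mixed ANOVA is applied to the outcome measures in general, and "Significance level will be set at 0.05 for all statistical tests". No variable, visit or contrast is designated as primary.

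The listed objectives give the only hint of timing: the first is to assess sitting balance once the 8 weeks of training are complete, which corresponds to T2.

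**The concern.** A reader of the sample-size section would expect one confirmatory test. A reader of the outcomes section would expect a family of them, including EMG and evoked-potential measures. The two readings imply different error control and different power, and the article does not choose between them.

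The trial cannot blind participants or assessors, as its Randomisation section says. Fixing the primary variable in advance is therefore one of the few protections left against emphasising whichever result turns out best. While the primary outcome stays a construct with many measures, a favourable result on any of them could be presented as the primary finding, although the stated power was worked out for one only.

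**Working it through.** **Step 1. Reproduce the plan's figure.** Inputs from the sample-size section: d = 0.85, 80% power, alpha 0.05, 1:1 allocation. Sidedness is not stated, so two-sided is taken. For a two-sample t-test with n = 23 per group, the degrees of freedom are 2 × 23 − 2 = 44 and the noncentrality is 0.85 × √(23/2) = 2.88. The noncentral t distribution gives power of 80.5%, and 23 is the smallest n per group that reaches 80%. A one-sided test would need 18. The stated 46 is therefore correct for a two-sided test of **one** variable.

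**Step 2. Count what stands under the primary heading.** The article gives no count, so two readings are shown.

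| Group | Named parameters | Split by task or direction |
|---|---|---|
| Sitting posture | 1 | 1 |
| Reaching distance | 1 | 2 (forward, lateral) |
| Trunk angular displacement | 1 | 2 (forward, lateral) |
| Shoulder range of motion | 1 | 1 |
| EMG amplitude and centroid | 2 | 2 × 5 tasks = 10 |
| Evoked-potential amplitude and latency | 2 | 2 |
| **Total** | **8** | **18** |

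**Step 3. Chance of at least one false positive.** Assume no true effect, one test per measure at 0.05, and one visit. Under independence the chance is 1 − 0.95^k:

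- k = 8: 1 − 0.95^8 = 0.337
- k = 18: 1 − 0.95^18 = 0.603

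The measures come from the same people and often the same tasks, so independence is the upper end. For a common correlation ρ, each test statistic was simulated as √ρ·W + √(1−ρ)·e, with W shared by all measures and e specific to each, and counted as significant beyond ±1.96 (400,000 draws). The article gives no correlations, so the values of ρ are assumptions.

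| ρ | 8 measures | 18 measures |
|---|---|---|
| 0 (formula) | 33.7% | 60.3% |
| 0.5 | 25.1% | 39.7% |
| 0.8 | 15.8% | 21.7% |
| 0.9 | 11.9% | 15.0% |
| 0.95 | 9.6% | 11.4% |

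**Step 4. What adjustment would cost if every measure stayed primary.** The t-test of Step 1 is repeated at d = 0.85 with a Bonferroni level.

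- 8 measures: 0.05/8 = 0.00625. Power at 23 per group is 51%, and 80% power needs 38 per group (76 evaluable).
- 18 measures: 0.05/18 = 0.00278. Power at 23 per group is 40%, and 80% power needs 43 per group (86 evaluable).

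With one primary variable the error is 5% and the result of Step 1 stands.

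**The case against.** The strongest reply is that an analysis plan may exist, and that multiplicity rules and the primary contrast commonly belong there. That is fair as far as missing detail goes, and the absence of an adjustment method is not the point here. What remains is a conflict inside the article: one section sizes the trial on a single primary measure, while another defines the primary outcome as several. An analysis plan cannot agree with both.

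Several stronger readings are tempting but not supported.

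- **That there are at least 18 primary measures.** The text names eight. Eighteen is a plausible expansion. The EMG section says that activity is recorded during the tasks, not that each task gives its own primary test.
- **That the false-positive rate is 60%.** That value needs both the larger count and independence, which is unlikely for measures taken from the same participants.
- **That any single significant result will count as success.** No success rule is stated, and the label of the second component suggests an explanatory role. The error rates are conditional on that reading.
- **That T2 and T3 will be tested separately.** The plan describes one repeated-measures ANOVA per outcome, with post hoc tests after a main effect. No inflation for a second visit is claimed here.
- **That nothing indicates the variable or the visit.** The sample-size section points to forward-reach trunk angle and the first objective points to T2. Both are indirect and neither overrides the outcomes section.

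**Conclusion.** The concern holds as an internal disagreement about what the primary outcome is, combined with a stated 0.05 for every test. If one significant measure is taken as primary success, the false-positive chance at one visit runs from about 12% to 34% for eight measures, and from about 15% to 60% for eighteen, as the correlation goes from 0.9 down to 0. These figures rest on an assumed common correlation and one test per measure. The exact size is uncertain, but the direction is not: even at a correlation of 0.95 the error is about twice the nominal 5%, at 9.6% or 11.4%. The 80% power statement is arithmetically right and applies to one variable only.

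**What to change.** State one primary endpoint: the between-group difference in trunk angular displacement during forward reaching at T2. It is the variable on which the trial was powered, and the visit matches the first objective. Make the other sitting-balance measures secondary, and the EMG and evoked-potential measures mechanistic secondary outcomes. Report these with 95% confidence intervals and no confirmatory claim, or with Holm adjustment within each family. Bring the sample-size, outcomes and statistical sections into line with this before outcome data are analysed.

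The cost is wording. No new data are needed, all measures are still collected and reported, and the evaluable N of 46 is unchanged. The real price is that no other measure can then be claimed as a primary success. If the sponsor prefers to keep the whole set as primary with Bonferroni adjustment, 76 evaluable participants (8 measures) or 86 (18) would be needed for 80% power at the same effect size.
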